#### Secondary outcomes: adolescent variables

Secondary outcomes include adolescent substance use and associated high risk behaviors (i.e., sexual risk-behavior, truancy, and criminal involvement). Analyses will compare trajectories of use over the post-discharge period, controlling for baseline status as a covariate. For each dependent variable, separate repeated measures Analysis of Covariance will test the influence of condition, controlling for the following covariates: baseline status on the dependent variable, baseline differences between groups, and any mental health or substance use treatment received over the follow-up period. The effect of PW dosage on each dependent variable will be calculated and partial eta squared (η2) will be used to estimate the proportion of variance caused by PW. The primary analytical goal will be to provide measures of association and 95% confidence intervals to reveal the effect size of PW on each dependent variable.

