Systematic reviews and meta-analyses of treatment approaches for adolescents with SUDs [28–31], including one conducted by this protocol’s Principal Investigator (PI; protocol first author) [32], have found that intervention models that include parents outperform other approaches and are supported by high quality evidence. In Kumpfer et al.’s [33] review of interventions for adolescents with SUDs, family-based interventions that involved a parent or caregiver had average effect sizes 2–9 times larger than adolescent-only interventions. A more recent meta-analysis by Tanner-Smith and colleagues [31] similarly found that family-based interventions outperformed other evidence-based behavioral treatment approaches. Numerous other studies have provided evidence that parent involvement in treatment can improve adolescent engagement, retention, and substance use outcomes [34–36]. This body of research provides justification for: (1) working with the parents of adolescents in residential treatment for SUDs and (2) for targeting parenting skills as a potential mechanism of change in adolescent SUD treatment outcome.

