### Study enrollment and randomization

In accordance with institutional review board procedures at Brown University and Rhode Island Hospital, parents of all newly admitted adolescents will receive a Consent to Contact (CoC) form as part of the standard intake process at the residential center. Parents that sign a CoC form will then be contacted by research staff in one of two ways. If the adolescent is admitted Monday through Friday during normal business hours (which accounts for about 80% of new intakes), research staff located on site will immediately approach the parents and invite them to initiate the consent process. If the adolescent is admitted after hours or on weekends, research staff will contact the parents using the preferred contact information provided.

Parents will provide written informed consent and adolescents will provide written assent in separate private rooms at the residential center. If an adolescent chooses not to participate, the parent will be given general feedback that the family did not qualify so as to protect the adolescent’s privacy. Parents and adolescents may choose to conduct the informed consent process and all other study procedures in English or Spanish.

Parents will be given the choice whether to return for the baseline assessment or complete it immediately following informed consent. In the Phase 2 trial, randomization will occur within 24 h after the baseline assessment. Parent-adolescent dyads will be randomized to either SC or PW+ using urn randomization balanced on sex, severity of substance use, and preferred language (English vs. Spanish). Randomization will be conducted by a Co-Investigator, not involved with the assessment process, as soon as a parent consents to participate. Condition assignments will be placed in sealed envelopes and given to the independent evaluator. The evaluator will give parents their sealed envelope indicating that their treatment condition immediately after completion of the baseline assessment. If the parent is assigned to PW+, the evaluator will schedule the first in-person coaching session.

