### Data analysis plan

All 60 parents will be included in statistical analyses consistent with an intent-to-treat (ITT) model. Prior to the main analyses, descriptive statistics will be run on key variables to examine distributional properties, identify outliers, and transform variables as needed. The two treatment conditions will be compared on baseline demographic and clinical variables using basic two-group independent sample t-tests. Using a *p* < .05 criterion, significant pre-existing baseline differences between conditions on any variables will be controlled in subsequent analyses.

GAIN-Q3 data will be entered into the GAIN’s proprietary software, which offers instant error checks and validation reports to prevent missing data. Other forms will be entered directly into study laptops using REDCap (Research Electronic Data Capture), a secure web-based application, to reduce missing data and entry errors. Attrition analyses will compare follow-up completers and non-completers on baseline clinical and demographic variables to determine if they differ systematically. If no systematic differences are found between completers and non-completers, then missing data will be estimated using multiple imputation methods with five datasets, an approach that has been shown to generate unbiased estimates when data are missing at random or missing completely at random [93].

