#### Putative mediators: parental communication and monitoring

The study will be underpowered to test mediation, but will examine the effects of PW on putative mediators. A repeated measures Analysis of Covariance will whether assignment to the PW+ condition has a significant effect on either of the putative mediators, controlling for any treatment received. In addition, we will calculate change in the putative mediators over each time interval as well as change in the dependent variables over each time interval. Correlations between change in the putative mediators and change in the dependent variables will be examined; significant positive correlations greater than *r* = .20 will be flagged as worthy of further analysis in a future trial. The goal of these analyses is to find promising trends to pursue in a larger fully powered trial.

For both the secondary outcome analyses and the mediator analyses, the investigators will also attempt to fit latent growth models to the data. Latent growth models represent a flexible approach to analyzing change that enable a comparison of conditions at each time point while accounting for the correlation of observations over time [94]. Although convergence is challenged in a small sample, latent growth models have been fit to samples as small as *n* = 22 [95, 96]. The study PI has conducted multiple analyses using latent growth models [32, 97, 98] and will lead the longitudinal analyses.

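### The only named models for the effect of condition adjust for treatment received after randomisation, so they need not estimate the effect of assignment to PW+

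*Protocol article*

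**What the plan says.** All places are in the protocol article.

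- **Analysis set (Data analysis plan).** "All 60 parents will be included in statistical analyses consistent with an intent-to-treat (ITT) model".
- **Secondary outcomes: adolescent variables.** A separate repeated measures ANCOVA for each outcome tests condition. The covariates are the baseline value of the outcome, baseline differences between the arms, "and any mental health or substance use treatment received over the follow-up period".
- **Putative mediators: parental communication and monitoring.** A repeated measures ANCOVA asks whether assignment to PW+ "has a significant effect on either of the putative mediators, controlling for any treatment received". The treatment is not defined further there; I take it to be the same follow-up treatment.
- **Timing (Study enrollment and randomization).** In Phase 2, "randomization will occur within 24 h after the baseline assessment", so treatment during follow-up comes after allocation.
- **Dosage (Secondary outcomes).** "The effect of PW dosage on each dependent variable will be calculated and partial eta squared" "will be used to estimate the proportion of variance caused by PW", with η2 in brackets between the two parts.
- **Use of the result (Sample size and power).** A small to medium effect, together with good feasibility and acceptability, is taken as support for a larger trial. The detected effect size then determines how many parents that trial needs.

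No condition model without the treatment covariate is named. Latent growth models are only to be attempted, and their covariates are not given.

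**The concern.** Randomisation makes the arms comparable on what precedes it. Treatment received during follow-up comes afterwards, and two routes could tie it to assignment.

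1. **PW+ to uptake.** The section Rationale for targeting parents cites evidence that "parent involvement in treatment can improve adolescent engagement, retention, and substance use outcomes". A programme meant to sustain parents' engagement after discharge could therefore alter how much outpatient care the adolescent receives. Holding uptake fixed would then remove whatever part of the effect runs through it. If uptake and outcome also share unmeasured causes such as severity, holding it fixed makes arms that were comparable no longer so.
2. **Outcome to uptake.** An adolescent who relapses may be sent back to treatment. The protocol does not say this, so it is an assumption. If it is true, the model conditions on a consequence of the outcome.

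At stake is the estimate that Secondary outcomes names as its main analytical goal, an effect size with a 95% confidence interval. That estimate feeds both the case for the next trial and its sample size.

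A lesser, related point concerns dosage. Parents work through PW at their own pace (PW online modules) and standard-care parents are not given it. Variance shared between dosage and outcome therefore cannot be called variance caused by PW.

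**Working it through.** **1. The plan's own figures.** Sample size and power gives 175 per group at d = 0.3 and 64 at d = 0.5, for power 0.8. Assuming two-sided alpha 0.05 and equal allocation, which are not stated with those figures:

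n per group = 2(1.960 + 0.842)²/d² = 15.70/d²

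This gives 175 at d = 0.3 and 63 at d = 0.5; the t-test version gives 175.4 and 63.8. The figures reproduce, so the sizing arithmetic is sound.

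**2. What the covariate does.** In a linear model,

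adjusted effect = total effect − a × g,

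where a is the difference between arms in treatment received and g is the slope of outcome on treatment received within arms. The two effects coincide when a = 0 or g = 0. The documents give neither quantity.

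**3. Illustration under assumed links.** Take a true total effect of -0.30 (negative means less use) and treatment received in SD units. Let a be 0 to 0.5, the effect of treatment on outcome b be -0.3 to +0.3, and the loading u of an unmeasured common cause on both treatment and outcome be 0 or 0.5. Then g = b + u², so

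adjusted = -0.30 − a(b + u²).

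Residual noise does not enter, so the outcome can be scaled to SD 1. A large-sample least-squares simulation agrees:

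| a | b | u | Formula | Simulated |
|---|---|---|---|---|
| 0 | any | any | -0.30 | -0.30 |
| 0.3 | -0.3 | 0 | -0.21 | -0.208 |
| 0.3 | -0.3 | 0.5 | -0.285 | -0.285 |
| 0.3 | 0 | 0.5 | -0.375 | -0.374 |
| 0.3 | +0.3 | 0 | -0.39 | -0.391 |
| 0.3 | +0.3 | 0.5 | -0.465 | -0.465 |
| 0.5 | -0.3 | 0 | -0.15 | -0.150 |
| 0.5 | +0.3 | 0.5 | -0.575 | -0.573 |

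The model without the covariate returned -0.30 in every row, within simulation error. When instead use drives uptake, a large-sample run with a true effect of -0.40 gave adjusted estimates of -0.36 to -0.30 across three assumed strengths.

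**4. Consequence for sizing.** Putting adjusted values into the formula of step 1, with SD 1:

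- d = 0.30: 175 per group
- d = 0.21: 356
- d = 0.15: 698
- d = 0.39: 104

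**5. Dosage.** Suppose PW has no effect, dosage correlates r with a prognostic factor, and that factor correlates 0.5 with outcome (all assumed). The shared variance is (0.5r)²: 1.0% at r = 0.2, 2.25% at r = 0.3 and 6.25% at r = 0.5. None of it is caused by PW.

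**The case against.** - **It is a pilot with feasibility and acceptability as primary outcomes.** This stands. None of those criteria uses an ANCOVA, and the protocol itself warns that effect sizes are unstable in small samples. With about 50 completers, 25 per arm, SD 1 and an assumed baseline correlation of 0.5, a single-time-point ANCOVA has SE = √[(1 − 0.25)(1/25 + 1/25)] = 0.245, hence a 95% interval of about ±0.48. Every shift in the table lies within that. It lowers the severity but does not remove the point, because noise averages out over trials and this bias does not.
- **No PW+ element is described as linking adolescents to care.** This is also fair. Coaching covers substance use, limit setting, monitoring and communication. The texts and board sustain use of PW. Discharge referral belongs to standard care, which both arms receive. The route from PW+ to uptake is plausible, not established.
- **The figures are not from the trial.** Correct. The calculation is a large-sample linear model for one outcome, whereas the plan is repeated measures with about 50 completers. The scenario in which use drives uptake speaks to substance use only, not to truancy, sexual risk, legal involvement or the mediators.
- **The dosage sentence may hold two separate items.** Partial eta squared may be meant for condition. As written it follows the dosage effect, so the wording needs correcting on either reading, but this is minor.

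A reader might also infer that the covariate contradicts the intent-to-treat statement. The text does not support that: the statement says that all 60 parents are analysed, and a covariate neither excludes nor reassigns anyone. The issue is which effect is estimated, not who is included.

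**Conclusion.** The point holds as a should-fix for the secondary and mediator analyses. The only named condition models adjust for a variable that arises after randomisation. Their coefficient equals the effect of assignment only if the arms do not differ in treatment received, or if treatment received is unrelated to outcome within arms. Otherwise it departs from that effect by a × g, in either direction.

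Under the assumed links a true -0.30 SD is reported as anything from about -0.15 to -0.57. These figures show sensitivity and do not predict this trial's result. A reader might conclude that every secondary and mediator estimate is distorted. The documents do not support that, since they give no uptake by arm and there is no bias if neither PW+ nor the outcome affects uptake. Nor do they support any effect on the primary feasibility and acceptability criteria.

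The consequence falls on the preliminary effect size and on the decision and sizing that rest on it. The dosage wording is a minor addition.

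**What to change.** 1. In both Secondary outcomes and Putative mediators, define the main condition model as adjusting for baseline variables only, and remove treatment received from its covariates.
2. Report mental health and substance use treatment received during follow-up by arm, as a descriptive outcome. This shows whether a difference in uptake exists.
3. Keep the treatment-adjusted model, labelled as exploratory or sensitivity, with a note that it does not estimate the effect of assignment.
4. State that the effect size carried into planning the larger trial comes from the model in item 1.
5. Report PW dosage as an association within the PW+ arm, say whether partial eta squared refers to condition or to dosage, and replace the causal phrase with one about variance associated with that term.

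The cost is a few sentences of analysis-plan wording. The plan already calls for treatment received as a covariate, so no new data, visits or participants are needed.

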#### Putative mediators: parental communication and monitoring

The study will be underpowered to test mediation, but will examine the effects of PW on putative mediators. A repeated measures Analysis of Covariance will whether assignment to the PW+ condition has a significant effect on either of the putative mediators, controlling for any treatment received. In addition, we will calculate change in the putative mediators over each time interval as well as change in the dependent variables over each time interval. Correlations between change in the putative mediators and change in the dependent variables will be examined; significant positive correlations greater than *r* = .20 will be flagged as worthy of further analysis in a future trial. The goal of these analyses is to find promising trends to pursue in a larger fully powered trial.

For both the secondary outcome analyses and the mediator analyses, the investigators will also attempt to fit latent growth models to the data. Latent growth models represent a flexible approach to analyzing change that enable a comparison of conditions at each time point while accounting for the correlation of observations over time [94]. Although convergence is challenged in a small sample, latent growth models have been fit to samples as small as *n* = 22 [95, 96]. The study PI has conducted multiple analyses using latent growth models [32, 97, 98] and will lead the longitudinal analyses.

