### Rationale for targeting parents

Parents have been established as a critical influence on adolescents’ initiation and maintenance of substance use [10], as well as their substance use outcomes and likelihood of relapse following treatment [11]. Two parenting processes that appear to be particularly important protective factors against adolescent SUDs are monitoring and supervision [12] and communication with the adolescent [13]. Parental monitoring has been identified as a pivotal factor in the initiation of adolescent substance use [10, 14–17] and several studies have implicated parental monitoring as a mechanism underlying adolescent substance use. For instance, one study of 4731 adolescents found that perceived parental monitoring had unique mediating effects on adolescent substance use [18], while other studies concluded that lax parental monitoring was one of the pathways through which parental substance use influenced adolescent substance use [19, 20]. Parental communication also appears to have important protective influences for adolescents with SUDs [10, 21, 22], with studies suggesting that the content, context, style and timing of communication about substance use are all important deterrents of use [23]. Several studies suggest that parenting interventions should target parent-teen communication about the parents’ attitudes toward substance use [24, 25]. One study [26] found that communicating strong parental norms against teen substance use reduced the risk of initiation in early adolescence, while two studies found that communicating disapproval of substance use predicted less alcohol use later in adolescence [24, 27].

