### Assessments

Parents and adolescents will complete a baseline assessment in-person shortly after their admission to residential treatment. Adolescents will be assured of confidentiality and a National Institute of Health Certificate of Confidentiality (CoC) will be obtained, as adolescent self-report use has shown reliability when confidentiality is assured [77–80]. The CoC will allow the research team to refuse to disclose names or other identifying characteristics of research participants in response to legal demands such as subpoena of records. Follow-up assessments will be conducted by an independent evaluator who is blind to condition. During the open trial, there will be follow-up assessment at 6 weeks post-discharge, while during the pilot randomized trial there will be three follow-up assessments at 6, 12, and 24 weeks post-discharge. Follow-up assessments will be scheduled in-person at the residential treatment center; if a parent no-shows more than twice for a follow-up assessment, then research staff will attempt to conduct the follow-up sessions at a location of the family’s choosing (i.e., home, school). The baseline assessment will be 1.5–2 h and the follow-up assessments will be about 1.5 h (see Table 3 for overview of measures).

**Table 3 Tab3:** Overview of protocol measures

Construct	Measurement/scale	Data obtained
Feasibility	Participation rates	Percent of parents who participate in the study
	Parent engagement	Number of coaching sessions attended, online usage of PW and parent message board (i.e., logins, sessions completed, page views, time spent), number of texts viewed
Acceptability	Withdrawal rates	Percent of parents who withdraw from study
	Exit interviews (open trial only)	Open-ended questions on perceptions of in-person sessions, text messages, computer program, and online message board
	CSQ	Satisfaction with treatment delivery and ability to manage their adolescent’s problems
Adolescent substance use	GAIN days of use	Days of alcohol use, marijuana use, and other drug use
	GAIN SFS	Averages percent of past 90 days during which there was use of alcohol, marijuana, or heavy drugs; intoxication; and failure to perform activities due to use
	Gain SUDS	Assesses substance use disorder symptoms in line with both DSM-IV and DSM-V criteria

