#### Sample size and power

The study will recruit 60 participants for the randomized trial. Estimating that 15–20% may be lost to follow-up, there will likely be 50 participants with complete parent-adolescent data. We will use these participants to make judgments regarding feasibility and acceptability. Effect size estimates in prior PW studies have ranged from small to very large; the only study conducted among adolescent substance users found small to medium effects, but unlike this application, that study did not offer in-person support or an online parent board (supports that may contribute to larger effect sizes). Furthermore, even small effects, if obtained by delivering content electronically via a highly scalable platform that can reach large numbers of parents, can have significant public health implications. Despite issues with effect size stability in small samples [99], a small to medium effect paired with high levels of feasibility and acceptability would therefore be an indication that the adapted PW intervention should be tested in a larger trial. Based on the detected effect size, post hoc power analyses will be conducted to determine the number of parents required for a fully powered trial. For instance, for power of .8, a small effect size (d = .3) would require a sample of 175 per group, while a medium effect size (d = .5) would require a much smaller sample of 64 per group.

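### The mediator screen flags only significant positive correlations: the wrong sign for the main pairings on raw scores, with an r = .20 cut-off made redundant by the significance condition

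*Protocol article*

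**What the plan says.** The rule is in the protocol article, section Putative mediators: parental communication and monitoring. First, "we will calculate change in the putative mediators over each time interval as well as change in the dependent variables over each time interval". Then: "Correlations between change in the putative mediators and change in the dependent variables will be examined; significant positive correlations greater than" r = .20 are to be flagged for a future trial. The same section concedes that the study is underpowered for mediation and says that the aim is to find promising trends.

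The expected direction is given under Rationale for targeting parents: "Two parenting processes that appear to be particularly important protective factors against adolescent SUDs are monitoring and supervision", with communication named as the second.

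The outcomes are set out under Secondary outcomes: adolescent variables ("Secondary outcomes include adolescent substance use and associated high risk behaviors") and in Table 3 of the Assessments section, for example "Days of alcohol use, marijuana use, and other drug use". Table 3 also lists the substance frequency scale, disorder symptoms, risky sexual behaviour and days of legal involvement. Its school item covers both attendance and truancy, and its communication scale covers both positive and negative aspects.

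On numbers, Sample size and power says that "there will likely be 50 participants with complete parent-adolescent data". The Data analysis plan section includes all 60 parents under intention to treat, with multiple imputation if completers and non-completers do not differ systematically.

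**The concern.** The rule has three parts: a sign, a significance condition and a size. Two of them look wrong.

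- **Sign.** If monitoring protects, then as monitoring rises, use should fall. The change-on-change correlation is then negative, and a rule that accepts only positive values selects the opposite pattern, in which more monitoring goes with more use.
- **Size.** With about 50 dyads, a correlation just above .20 does not reach conventional significance, so the stated cut-off may do no work.

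The screen exists to choose which parenting processes a larger trial should pursue, and those processes are the intervention's stated targets. A rule that passes over the hypothesised mechanism, or discards the modest trends it was meant to keep, defeats that purpose.

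**Working it through.** **Inputs**

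- Rule: significant, positive, r > .20 (Putative mediators section).
- Sample: 15–20% loss from 60 gives 60 × .85 = 51 and 60 × .80 = 48, which agrees with the protocol's figure of about 50. I take n = 50, with n = 60 (the full intention-to-treat sample) as the upper bound.
- Alpha: .05 is an assumption. The protocol states p < .05 only for baseline comparisons. Two-sided and one-sided values are both shown.
- The .20 cut-off is stipulated without derivation, so there is nothing to reproduce for it.

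**Step 1: expected sign on raw scores.** This assumes that a higher monitoring score means more monitoring, which the article does not state.

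| Mediator score | Outcome | Sign if the mediator works | Can the literal rule flag it? |
|---|---|---|---|
| Monitoring, positive communication | Days of use, substance frequency, symptoms, sexual risk, legal days, truancy days | Negative | No |
| Monitoring, positive communication | Attendance days | Positive | Yes |
| Negative communication | Days of use and the other harms | Positive | Yes |
| Negative communication | Attendance days | Negative | No |

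No single sign fits every row, and the first row holds the main pairings.

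**Step 2: smallest significant correlation.** r_crit = t / √(n − 2 + t²), with t the critical value on n − 2 degrees of freedom.

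- n = 50, two-sided: 2.011 / √(48 + 4.043) = .279. One-sided: .235.
- n = 60, two-sided: 2.002 / √(58 + 4.007) = .254. One-sided: .214.
- At the ends of the 48–51 range, two-sided: .285 and .276.

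Conversely, r = .20 at n = 50 gives t = .20 × √(48 / .96) = 1.414, two-sided p = .164 (one-sided .082). At n = 60 the two-sided p is .126 (one-sided .063). A correlation of .20 first becomes significant at n = 97 two-sided or n = 69 one-sided. Under every one of these choices the significance condition is the stricter one, so .20 never decides anything.

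**Step 3: chance of a flag.** Fisher z, standard error 1/√(n − 3); n = 50, two-sided .05. Here atanh(.2787) = .286 and √47 = 6.856.

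- True r = −.40 (atanh = −.424). Literal rule: z = (.286 + .424) × 6.856 = 4.87, probability about 0. Rule in the hypothesised direction: z = (.424 − .286) × 6.856 ≈ .94, probability about .83.
- True r = −.30. Literal rule: about .00002. Hypothesised direction: about .56.

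**The case against.** The best defence is that positive may mean that both variables improve. If both changes are scored as improvement, the sign is right, and scoring direction is the sort of detail an article may leave to a fuller document. This stands as a possible reading. It does not remove the point, because the article itself states the sign, speaks plainly of change in each variable, and nowhere says that scores are reversed.

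Several stronger readings are tempting, and the documents do not support them.

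- A reader might infer that a working mediator can never be flagged. Attendance days and negative-communication scores could be flagged correctly even on raw scores.
- A reader might infer that the rule is unattainable or that its parts contradict each other. They form a coherent joint condition: at n = 50 and two-sided .05 it reduces to r of at least .279, and a true +.30 or +.40 would be flagged about 56% or 83% of the time. The cut-off is redundant, no more. If the test is one-sided, the gap narrows to .235, or to .214 with 60 dyads.
- A reader might infer that changes are paired within the same interval, so that temporal order is lost. The text does not say how intervals are paired, and it makes no claim about order.
- A reader might put a number on chance flags. That depends on how many scores are tested, which the article does not fix.

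It is also fair to say that all the correlations are to be examined, so a strong negative one would be seen even if unflagged. The statement under Sample size and power on going to a larger trial rests on effect size, feasibility and acceptability, not on this flag.

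**Conclusion.** The point holds, at moderate severity. Followed literally, the rule does not flag the hypothesised pattern for substance use, sexual risk and legal involvement: about 0% against about 83% for a true correlation of −.40 in 50 dyads. Separately, correlations from .20 up to the critical value (.279 with 50 dyads, .254 with 60, two-sided) cannot be flagged, although the screen is meant to find promising trends.

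The sign result assumes raw, unreversed scores and a monitoring score that rises with monitoring. The cut-off result assumes alpha .05 and one independent observation per dyad per interval.

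The analysis is an exploratory screen under the third aim of a pilot. The error affects which mediators are carried forward. It does not touch the primary feasibility and acceptability outcomes or the estimates of effect on adolescent outcomes, so it does not warrant the highest severity.

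**What to change.** Amend the rule in two respects.

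1. Orient each mediator and outcome score so that a positive change means improvement, or list the hypothesised sign for each pairing. Attendance, truancy and the positive and negative communication scores need this explicitly, and it should be settled before the data are seen.
2. Drop the significance condition and flag r ≥ .20 in the hypothesised direction, reporting each correlation with its 95% confidence interval.

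This takes about two sentences and no new data. At n = 50 a true correlation of .30 in the hypothesised direction would then be flagged with z = (.310 − .203) × 6.856 ≈ .73, or about 77% of the time, against about 56% with the significance condition kept.

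The cost is more chance flags. For a pairing with no true correlation, the rate rises from 2.5% (one tail of a two-sided .05 test) to about 8.2% at n = 50, or 6.3% at n = 60. The reported intervals make that uncertainty visible, which suits a screen for trends.

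Lagging the intervals, partialling out condition, or restricting the screen to one outcome are optional design choices and are not needed to correct this error.
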